## Study procedures

TFEQ

Eating behaviour is evaluated using in a Dutch translation of the three-factor eating questionnaire (TFEQ). This validated questionnaire consists of three subscales: cognitive restraint of eating, disinhibition of dietary restraint and emotional eating and perceived hunger (24).

Baecke questionnaire

Habitual physical activity is evaluated using a Dutch translation of the Baecke questionnaire. This questionnaire consists of three subscales: work activity, sports activity and non-sports leisure activity (27).

Blood samples

On the day of the screening a blood sample (10 ml) will be collected via vena puncture in the antecubital vein in a 10 ml EDTA tube. From the peripheral blood leukocytes from the blood DNA will be isolated and certain SNPs will be genotyped. Genotyping will be performed using commercially available TaqMan SNP genotyping assays according to the manufacturer’s protocol. The following SNPs will be determined:

- FTO rs9939609 A allele (4-8, 26, 28)
- MC4R rs7782313 C allele (29-32)
- PPAR2 Ala12 allele (9, 10, 15)
- ADRB2 Gly16 allele (33, 34)
- PLIN 11482 A allele (12, 13)
- UCP1 A3826 A allele (35, 36)

Subjects’ blood lipid profile (triacylglycerols (TAG), free fatty acids (FFA), total cholesterol, HDL, and LDL) and glucose homeostasis (glucose, insulin, and HbA1c) will be determined. For this, 10ml blood will be collected in an EDTA tube. In total 20 ml blood will be taken per subject ones. Blood samples will be stored at - 80C until analyses.

Body composition

Subjects’ body composition will be calculated from body volume and total body water using the combined equation of Siri (37). Body volume is measured with a BodPod. Total body water is measured with Deuterium dilution according to the Maastricht protocol (38). Subjects drink a Deuterium dilution (about 70 g with an enrichment of 5 atom% excess 2H) in the evening prior to the measurements after the collection of a baseline urine sample. The next morning after a 10-hour equilibration period, where subjects are not allowed to eat or drink, a second urine sample is collected.

Physical activity

Habitual physical activity will be measured using a triaxial accelerometer for movement registration (TracmorD; DirectLife, Philips new wellness solutions, Amsterdam, The Netherlands) sensitive to a wide range of body movements. The accelerometer has been validated with doubly labelled water, the gold standard for measuring energy expenditure in daily life (39). To ensure a valid reflection of long-term daily life activities, the accelerometer will be worn for a period of 14 days under free-living conditions. Subjects will be instructed to wear the TracmorD from the moment they wake up in the morning until they go back to bed at night. The TracmorD is only a small device that will be worn on a belt around the waist. To verify whether subjects live up to this instruction, waking hours and clock times of wearing the TracmorD have to be noted. Subjects will wear this device during the fist two weeks of the weight loss period, the first two weeks of the weight maintenance period and the last two weeks of the experiment.

MEASUREMENTS ONLY FOR GROUP WITH HIGH AND LOW PREDISPOSITION FOR WEIGHT REGAIN

Fat biopsy

Abdominal fat biopsies are obtained by needle liposuction under local anesthetics (lidocain 2% with adrenalin 1:80000, AstraZeneca BV, Nederland) after an overnight fast.

Adipocytes will be isolated from the fat biopsies for determination of adipocyte cell size via a standard protocol (described in (40)). In short, DNA will be quantified for determining the amount of adipocytes in the biopsy. In addition, the triacylglycerol (TAG) content in the biopsy will be determined. Then, the mean adipocyte cell size can be calculated as g TAG/cel (mean DNA content per cell is 6pg).

Energy expenditure

Subjects will visit the university and will stay in a respiration chamber for one night to measure sleeping metabolic rate and part of the next day to measure basal metabolic rate and body composition for three times (before weight loss, after weight loss, 10 months maintenance). For female subjects this test will always take place in the same period of the menstrual cycle. Subjects enter the respiration chamber in the evening of day 1 at 19:00h and leave the chamber at 07:00h the following day. For details about each aspect of this protocol see below.

Indirect calorimetry

Oxygen consumption and carbon dioxide production will be measured in the respiration chamber. The respiration chamber is a 14m3 hotel room, furnished with a bed, chair, computer, television, radio, dvd-player, telephone, intercom, sink and toilet. The room is ventilated with fresh air at a rate of 70-80 l/min. The ventilation rate is measured with a dry gas meter. The concentrations of oxygen and carbon dioxide will be measured using a paramagnetic O2 analyzer and an infrared CO2 analyzer. During each 15-min period six samples of outgoing air for each chamber, and one sample of fresh air, zero gas, and calibration gas will be measured. The gas samples to be measured will be selected by a computer that also stores and processes the data. Metabolic rate is calculated using Weir’s formula (41).

Sleeping metabolic rate

Sleeping metabolic rate (SMR) is defined as the mean metabolic rate during three consecutive hours between 00:00h and 07:00h with most stable energy expenditure.

Basal metabolic rate

The following morning when leaving the respiration chamber in a fasted state, the subjects go immediately under a ventilated hood to measure basal metabolic rate. After 15 min resting, basal metabolic rate will be measured by means of an open circuit ventilated hood system with subjects lying supine for 30 min (42). Gas analysis is performed by a paramagnetic oxygen analyzer (omnical type 1155B, Crowborough Sussex, UK) and an infrared carbon dioxide analyzer (omnical type 1520/1507).

After the ventilated hood measurement the subjects’ body composition will be determined and a fat biopsy will be taken as described above. After all these measurements the subjects will receive a breakfast before they are sent home. The subjects will be able to choose from several food items, unless they are in the weight loss program where they only receive the VLED (Modifast). All foods will be prepared in a research kitchen from the Department of Human Biology by one of the researchers.

Total energy expenditure

Total energy expenditure will be measured with the doubly labelled water (DLW) technique following the Maastricht protocol [30]. Subjects will have to collect a background urine sample immediately before isotope consumption to correct for isotopic backgrounds. Subsequent urine samples will be collected from the second and last voiding of the first, 8th and last day of a 14-day period. Isotope enrichment of the urine samples will be analyzed with isotope ratio mass spectrometry.

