
Genes interact with and exert their effects on various biological, behavioral and environmental factors, thereby influencing body weight and composition. It has been hypothesized that a reduced capacity to oxidize fat is involved in the development of obesity (1). Rats with inherited susceptibility to diet-induced obesity showed a reduced capacity for fat oxidation than rats resistant to diet-induced obesity (17). It has been suggested that the susceptibility to diet-induced obesity was based on a limitation in transporting fatty acids into hepatocytes an in initiating -oxidation of fatty acids. Also, the partitioning of dietary fat between tissues might play a role in the susceptibility to obesity (18). It has been shown that dietary fat oxidation is negatively related to body fatness, in which obese individuals showed the lowest fat oxidation (19). In obesity-prone rats weight regain after weight loss was accompanied by reduced oxidation of dietary fat and the formation of new adipocytes (20). In addition, with weight loss a major saving on energy expenditure has been found, mainly caused by a reduction in physical activity (1). This decrease in activity energy expenditure during energy restriction is difficult to overcome with exercise training (21). Resting energy expenditure (REE) and sleeping metabolic rate (SMR) has been shown to decrease during weight loss, but whether this also holds during weight maintenance is still subject of debate (22, 23). Finally, weight loss maintenance has been shown to depend largely on psycho-behavioural factors such as eating behaviour. These factors are also influenced by, and interact with genes. Like the disinhibition score as defined by the Three Factor Eating Questionnaire (TFEQ; (24)), was strongly linked to the gene coding for PPAR (3, 25). All these factors are likely to change during weight loss and maintenance. Therefore, adipogenic capacity, energy expenditure, physical activity and behavioural factors should all be investigated in a weight loss and maintenance experiment.

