|  | **Screening** | **Pre-weight loss** | **Weight reduction program (2 months)** | **Post-weight loss** | **Weight maintenance program (10 months)** | **Post-weight maintenance** |
| --- | --- | --- | --- | --- | --- | --- |
| Measurements |  | Month 0 | Month 1 | Month 2 | 3 months after start maintenance | 10 months after start maintenance |
| **Body weight**  **Height**  **Body mass index**  **Waist/Hip** | X  X  X  X | X  X  X | X  X  X | X  X  X | X  X  X | X  X  X |
| **TFEQ**  **Baecke** | X  X | X  X | X  X | X  X | X  X | X  X |
| **Total body water**  **Body density** |  | X  X |  | X  X | X  X | X  X |
| **Physical activity** |  | X |  | X | X | X |
| **Blood parameters**  **Polymorphisms** | X  X |  |  |  |  |  |
| **Time** | 45 min | 60 min | 20 min | 60 min | 60 min | 60 min |

Fig 3. Measurements for the group with medium predisposition for weight regain. Three Factor Eating Questionnaire (TFEQ).

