# TREATMENT OF SUBJECTS

## Investigational product/treatment

All subjects undergo a weight loss program, which consists of a very low calorie diet (VLED; Modifast) containing 2.1MJ/d for 2 months. There are no risks for the subjects in consuming the VLED (Modifast, together with the recommended fruit and vegetables) as the macronutrient composition and vitamins/minerals content meet the Dutch recommended daily allowance.

Deuterium is an isotope of water that naturally appears in the body. Drinking it does not expose the subject to any risks. The doubly labelled water is safe to use in humans since the water is labelled with stable isotopes. The concentrations of the samples are far below 10000 ppm or 1%, where effects on biological systems have been observed.

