# METHODS

## Study parameters/endpoints

### Main study parameter/endpoint

The role of the genetic background involved in weight regain through mechanisms including energy expenditure, physical activity and adipogenic capacity.

Energy expenditure (see fig 2, page 13, and page 21 and 22 for detailed description) will be determined via three measurements. First, the respiration chamber measurements, which will determine oxygen consumption and carbon dioxide production overnight to determine sleeping metabolic rate. Second, the ventilated hood measurements in the mornings to determine basal metabolic rate. And the last measurement is the use of doubly labelled water to determine total energy expenditure. These measurements will be performed before and after weight loss, and after weight maintenance.

Physical activity (see fig 2+3 on page 13+14, and page 20 for detailed description) will be determined via a triaxial accelerometer, which ensures movement registration sensitive to a wide range of body movements, thereby determining habitual physical activity. These measurements will be performed before and after weight loss, and after weight maintenance.

Adipogenic capacity (see fig 2, page 13, and page 21 for detailed description) will be determined via measurements on number and size of fat cells from fat biopsies. These measurements will be performed before and after weight loss, and after weight maintenance.

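### The first accelerometer fortnight falls inside the very low energy diet, so physical activity has no pre-diet recording although section 7.1.1 calls for one; the number of recordings also differs between sections

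*Protocol*

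**What the plan says.** Four places in the Protocol give the timing of the physical activity measurement.

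- **Section 7.3, Physical activity.** Each recording is long: "the accelerometer will be worn for a period of 14 days under free-living conditions". The first window is on the diet: "Subjects will wear this device during the fist two weeks of the weight loss period". The second is the opening fortnight of maintenance and the third is the final fortnight of the experiment. That makes three windows, and the list reads as complete.
- **Section 7.1.1, physical activity paragraph.** "These measurements will be performed before and after weight loss, and after weight maintenance". That is also three occasions, but the first is before weight loss.
- **Section 3, Figs 2 and 3.** The row in both schedules is "Physical activity | | X | | X | X | X". The marks fall under pre-weight loss (Month 0), post-weight loss (Month 2), and 3 and 10 months after the start of maintenance. The weight-reduction column is blank. That makes four occasions.
- **Section 5.1.** The diet in force throughout the weight-loss period is described as "containing 2.1MJ/d for 2 months", for all subjects.

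The introduction says that the energy saving seen with weight loss comes mainly from reduced physical activity. It adds: "This decrease in activity energy expenditure during energy restriction is difficult to overcome with exercise training". Physical activity is one of the mechanisms named in the main study parameter (7.1.1) and in the primary objective (section 2).

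**The concern.** A value meant to represent habitual activity before weight loss would be recorded while subjects are on the diet, a state in which the protocol itself expects activity to be lower. Any part of the fall that has already happened in that fortnight is built into the baseline and disappears from the measured change. Later analysis cannot recover it, because the recording before the diet would never have been made.

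The number of recordings is a separate problem. Staff who follow 7.3 would collect no accelerometer data at 3 months of maintenance. Staff who follow the figures would.

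**Working it through.** **Step 1. The sources side by side.**

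| Source | Before diet | First 2 weeks of diet | After weight loss | 3 months of maintenance | End |
| --- | --- | --- | --- | --- | --- |
| 7.1.1 | yes | no | yes | no | yes |
| 7.3 | no | yes | yes (first 2 weeks of maintenance) | no | yes (last 2 weeks) |
| Figs 2 and 3 | yes (Month 0) | no | yes (Month 2) | yes | yes |

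The sources disagree on the first occasion (7.3 against the other two) and on the 3-month occasion (the figures against the other two). No other section supplies an accelerometer period before the diet.

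**Step 2. Position of the first window.** Two months is about 56 to 61 days. The window covers 14/61 = 23% to 14/56 = 25% of the diet, and no day of it lies before the diet.

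**Step 3. Effect on change from baseline.** Set true habitual activity before the diet to 1. Let f be the proportional fall during the first diet fortnight and c the true proportional fall at follow-up. The recorded baseline is 1 - f and the recorded follow-up is 1 - c, so

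apparent change = (1 - c)/(1 - f) - 1.

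The protocol gives the direction of the fall but no value for f or c. Both are assumptions, shown over a range.

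| Assumed early fall f | True change 0% (c = 0) | True change -10% (c = 0.10) |
| --- | --- | --- |
| 0% | 0.0% | -10.0% |
| 5% | 1/0.95 - 1 = +5.3% | 0.90/0.95 - 1 = -5.3% |
| 10% | 1/0.90 - 1 = +11.1% | 0.90/0.90 - 1 = 0.0% |
| 20% | 1/0.80 - 1 = +25.0% | 0.90/0.80 - 1 = +12.5% |

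An early fall as large as the later one removes the measured change, and a larger one reverses its sign. The same formula applies to the change across weight loss and to the change from baseline to study end.

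**Step 4. Effect on the genotype contrast.** Work in absolute activity units, with f and c now the falls in those units. The measured change in a group is f - c instead of -c. The difference in change between the high and low groups is therefore

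(f_high - f_low) - (c_high - c_low),

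and the bias is f_high - f_low. It is zero when the early fall is the same in both groups.

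**Step 5. Change within maintenance.** This is the last window minus the window at the start of maintenance. The first window does not enter, so f has no effect.

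**The case against.** Several points can be made for the plan as it stands.

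- **The figures list visits, not recording periods.** A 14-day recording cannot fit into a visit of 60 minutes or 16 hours, so the Month 0 mark may mean that the device is handed out then. This is a fair reading and it softens the conflict with Figs 2 and 3. It does not reconcile 7.3 with 7.1.1, and it would confirm that nothing is recorded before the diet.
- **There is a pre-diet activity measure.** The Baecke questionnaire is completed at screening and at Month 0 in all groups. A reader might infer that no activity baseline exists at all, and that would be wrong. But Baecke is self-report, and 7.1.1 names the accelerometer for this endpoint.
- **The contrast closest to the objective survives.** Section 2 asks about the response to a maintenance period after weight reduction. For activity that is the start of maintenance against its end, and 7.3 collects both. This stands. A reader who concluded that all activity comparisons are spoiled would go beyond the documents.
- **Bias between genotypes is not shown.** It is tempting to argue that FTO acts on appetite and that the early fall must therefore differ by genotype. The introduction links FTO to hunger and satiety, and its activity associations concern other genes. The documents supply no route to a differential early fall, so this remains a condition and not a finding.
- **Size and onset are unknown.** The introduction supports a fall during restriction but does not say how much of it occurs in the first 14 days. That the baseline is already lowered is a likely inference, not an established fact.

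A reader might also take the 3-month point to be the only activity measure in maintenance. It is not: 7.3 has windows at the start and end of that period, and Baecke is scheduled at 3 and 10 months. It is the only accelerometer point between those two windows.

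**Conclusion.** Section 7.3 is wrong as written. Followed literally, it leaves a named main parameter without the pre-weight-loss recording that 7.1.1 specifies, and the loss is permanent once the diet starts.

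The harm is confined to comparisons that use the first window: the change across weight loss and the change from baseline to study end. A fall in activity is likely to be under-measured there. Its size cannot be taken from the documents. Under the assumed true fall of 10%, the apparent change runs from -5.3% to +12.5% as the early fall runs from 5% to 20%. This rests on the protocol's own statement about direction and on the assumption that part of the fall occurs within the first fortnight. With no early fall there is no bias.

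The disagreement between three and four recordings also stands and needs one answer.

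**What to change.** 1. In 7.3, move the first 14-day wearing period to before the start of the diet, after eligibility is confirmed. Keep the windows at the start of maintenance and at the end of the experiment.
2. Make 7.1.1, 7.3 and Figs 2 and 3 state the same windows. Either add the 3-month recording to 7.1.1 and 7.3 or remove it from the figures; both reconcile the text. State in the figures whether a mark means device hand-out or recording.
3. Section 7.3 gives no start date for the 14-day doubly labelled water period. If its first value is to serve as the pre-weight-loss value, as 7.1.1 and Fig 2 imply, state that this period also ends before the diet starts.

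**Cost.** The device is handed out earlier, and the start of the diet may be delayed by up to two weeks. Because section 4.1 checks eligibility after the screening measurements, earlier hand-out may need one contact beyond the six visits in the Summary, or an earlier Month 0 visit. The doubly labelled water dose would have to be given early enough for its 14 days to finish before the diet, which may also move that visit. Keeping the 3-month recording adds one wearing period that the schedules already show.

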# STUDY DESIGN

Subjects screened for participation

Subjects excluded because they did not met inclusion criteria

Subjects included follow weight loss program

2 months (n = 200)

Highest predisposition for weight regain-group (n = 40)

 All measurements

Lowest predisposition for weight regain-group (n = 40)

 All measurements

Weight maintenance period of 10 months

Medium predisposition for weight regain (n = 120)  limited measurements

Fig 1. Flow of participants through the study

Subjects will be assigned to a subgroup based on their genetic profile, which will be determined with genotyping analysis from the blood drawn during the screening (for detail see section 7.3). The three groups will consist of subjects with a high predisposition for weight-regain, a low predisposition for weight regain and all subjects in between. All subjects undergo a weight loss program, followed by a weight maintenance period. The subjects in the group of low and high predisposition for weight regain will be studied more thoroughly, while the others will only undergo the more basal measurements. Figure 2 and 3 give an overview of all the measurements that will be done in the groups with a high/low predisposition for weight regain and the group with medium predisposition respectively (for details of the measurements see section 7.3).

|  | **Screening** | **Pre-weight loss** | **Weight reduction program (2 months)** | **Post-weight loss** | **Weight maintenance program (10 months)** | **Post-weight maintenance** |
| --- | --- | --- | --- | --- | --- | --- |
| Measurements |  | Month 0 | Months 1 | Month 2 | 3 months after start maintenance | 10 months after start maintenance |
| **Body weight**  **Height**  **Body mass index**  **Waist/Hip** | X  X  X  X | X  X  X | X  X  X | X  X  X | X  X  X | X  X  X |
| **TFEQ**  **Baecke** | X  X | X  X | X  X | X  X | X  X | X  X |
| **Total Body Water**  **Body density** |  | X  X |  | X  X | X  X | X  X |
| **SMR**  **BMR** |  | X  X |  | X  X |  | X  X |
| **Physical activity** |  | X |  | X | X | X |
| **Doubly labelled water** |  | X |  | X |  | X |
| **Blood parameters**  **Polymorphisms** | X  X |  |  |  |  |  |
| **Adipocytes** |  | X |  | X |  | X |
| **Time** | 45 min | 16h | 20 min | 16h | 60 min | 16h |

Fig 2. Measurements for the group with a high and low predisposition for weight regain. Three Factor Eating Questionnaire (TFEQ), Sleeping metabolic rate (SMR), basal metabolic rate (BMR).

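### The first accelerometer period is set on the diet in section 7.3 but before weight loss in section 7.1.1 and Figs 2 and 3, and the 3-month measurement in the figures has no wear period

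*Protocol*

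**What the plan says.** Protocol section 7.3 (Study procedures, Physical activity) fixes the wear periods. For the first it says: "Subjects will wear this device during the fist two weeks of the weight loss period". The other two are the opening fortnight of maintenance and the closing fortnight of the study. That makes three periods. The same paragraph states their purpose: "To ensure a valid reflection of long-term daily life activities, the accelerometer will be worn for a period of 14 days under free-living conditions". Section 5.1 defines the weight loss programme as 2.1 MJ/d for 2 months, so the first period lies wholly on the diet.

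Section 7.1.1 says of physical activity: "These measurements will be performed before and after weight loss, and after weight maintenance".

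Figs 2 and 3 in section 3 carry the same row for all three genotype groups: "Physical activity | | X | | X | X | X". Read against the column heads, the marks fall at pre-weight loss (Month 0), post-weight loss (Month 2), 3 months into maintenance and 10 months into maintenance. Screening and the weight-reduction column are empty.

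Section 1 (Introduction and rationale) states that "with weight loss a major saving on energy expenditure has been found, mainly caused by a reduction in physical activity". It adds that activity energy expenditure decreases while energy is restricted.

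**The concern.** Physical activity is named in the primary objective and is one of the mechanisms in the main endpoint. The accelerometer is the instrument that 7.1.1 assigns to it. Staff issuing devices will follow 7.3, because section 3 and section 7.1.1 both send the reader elsewhere for the detail and only 7.3 gives dates. The value used as baseline would then be recorded under a condition that the protocol's own rationale expects to lower activity. It would not represent the habitual daily life that 7.3 sets out to capture.

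The second wear period falls after the diet has ended. A before-to-after comparison would therefore set an on-diet fortnight against an off-diet fortnight, which mixes the state of being on the diet with the effect of having lost weight. Sleeping and basal metabolic rate are stated to be taken before weight loss, so two mechanisms in the same endpoint would start from different states. A pre-diet recording cannot be obtained once the diet has begun.

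**Working it through.** **Setting the places side by side**

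| Occasion | 7.1.1 | Figs 2 and 3 | 7.3 |
|---|---|---|---|
| Before the diet | yes | yes (Month 0) | no |
| First two weeks of the diet | no | no (column blank) | yes |
| After weight loss | yes | yes (Month 2) | yes (first two weeks of maintenance) |
| 3 months into maintenance | no | yes | no |
| End of maintenance | yes | yes (10 months) | yes (last two weeks) |

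There are two conflicts: the first occasion, and the 3-month occasion. The figures mark four measurements where 7.3 gives three wear periods.

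**What the first conflict does to each comparison**

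The protocol gives no figure for activity, so there is none to reproduce. Its sample size rests on resting energy expenditure and does not enter here. Write A0 for true pre-diet activity, A1 for the mean over diet days 1 to 14, A2 for the first two weeks of maintenance and A3 for the last two weeks of the study. Let E = A0 − A1 be the change already present in the first diet fortnight.

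- Baseline to after weight loss: true fall D = A0 − A2. Under 7.3 the measured fall is A1 − A2 = D − E. With f = E/D, measured fall = (1 − f) × D.
- Baseline to end of study: measured fall A1 − A3 = (A0 − A3) − E, so the error is the same E.
- Start of maintenance to end of study: A2 − A3 does not contain A1, so there is no error.
- Genotype contrast in a change from baseline: the error is E(high) − E(low), which is zero if the early reaction to the diet is the same in both groups.

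**Range for f**

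The documents give neither the size nor the speed of any fall, so every value of f below is an assumption.

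| Assumption | f | Measured fall as share of true fall |
|---|---|---|
| No early fall | 0 | 100% |
| Linear fall over 60 days, mean of days 1–14 at about day 7: 7/60 | 0.117 | 88.3% |
| Linear fall over 56 days: 7/56 | 0.125 | 87.5% |
| A quarter of the fall is early | 0.25 | 75% |
| Half of the fall is early | 0.5 | 50% |
| The whole fall is immediate | 1 | 0% |

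If activity recovered once the diet ended, so that E exceeded D, f would be above 1 and the measured change would reverse sign. If subjects became more active at the start of the diet, f would be negative and the fall would be overstated. The documents exclude neither case.

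**The case against.** The strongest reply is that this is one stray sentence. Section 7.1.1 and both figures place the measurement before weight loss, so the intention is clear. This stands in part. A reader might infer from 7.3 that an on-diet baseline is the settled plan and that the fall in activity will be understated. The documents do not support that: they contradict themselves, and the bias arises only if 7.3 is followed. Nor can the sentence be ignored, because it is the only text with dates. A device handed out at the Month 0 visit and worn for the next 14 days could even seem to satisfy the Month 0 mark, while giving no pre-diet record if the diet starts that day.

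A second reply is that pre-diet activity is measured anyway. This also stands in part. The Baecke questionnaire is completed at screening and is marked again at Month 0, so it would be wrong to say that subjects have no pre-diet activity value at all. It is self-report, however, and does not replace the accelerometer recording.

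A third reply is that the primary objective concerns the response to the maintenance period. The change over maintenance uses the other two wear periods and is untouched. That stands, and it limits the harm to changes measured from baseline. A reader might also infer that the genotype comparison is distorted. That needs an early reaction that differs by genotype, on which the documents are silent.

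The contrast with energy expenditure is clear only for sleeping and basal metabolic rate. For doubly labelled water, 7.3 gives a 14-day period without placing it relative to the start of the diet.

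**Conclusion.** The point holds as an internal contradiction with a conditional bias, and it should be resolved before the first subject starts the diet. Followed as written, 7.3 leaves all 200 subjects without a pre-diet accelerometer value for a mechanism named in the main endpoint, and leaves the 3-month measurement in the figures without a wear period.

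The understatement rests on two assumptions: that 7.3 is what staff follow, and that activity falls within the first two weeks of the diet. The rationale supports the direction of the second but gives no timing or amount. The shares tabulated above show only how the result depends on f. They are not estimates, and no percentage should be attached to this finding.

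**What to change.** In section 7.3, set the first wear period as 14 days completed before the diet starts, to agree with 7.1.1 and the Month 0 mark in Figs 2 and 3. If wear in the first diet fortnight is also wanted, label it 'during weight loss' and state that it is not used as baseline. Then either add a wear period at 3 months of maintenance to 7.3, or remove that mark from both figures. If the 3-month measurement is kept, 7.1.1 should list it too.

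The text change is small. In practice, devices must be issued after eligibility is confirmed and at least 14 days before the diet starts. The protocol does not give the interval between screening and Month 0, so this may need posting or a brief extra contact. A 3-month period, if kept, adds one further fortnight of wear per subject.

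### Fat-cell number is named as an endpoint, but the only number the protocol derives is the count in the needle aspirate, which does not measure the subject's adipocyte number

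*Protocol*

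**What the plan says.** Section 7.1.1 lists adipogenic capacity among the "mechanisms including energy expenditure, physical activity and adipogenic capacity" that make up the main endpoint, and the primary objective names it too. The same section says that it "will be determined via measurements on number and size of fat cells from fat biopsies", before weight loss, after weight loss and after maintenance. Number is therefore a named component beside size.

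The laboratory derivation is in section 7.3, under Fat biopsy:

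- Sampling: "Abdominal fat biopsies are obtained by needle liposuction under local anesthetics". No target amount or recorded weight is given.
- Purpose: "Adipocytes will be isolated from the fat biopsies for determination of adipocyte cell size via a standard protocol", with a citation to reference 40.
- Count: "DNA will be quantified for determining the amount of adipocytes in the biopsy", with the conversion "mean DNA content per cell is 6pg".
- Lipid: "the triacylglycerol (TAG) content in the biopsy will be determined".
- Size: TAG divided by the number of cells.

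The same section states that "body composition will be calculated from body volume and total body water". Fig 2 schedules body water and body density at all three biopsy visits in the high and low predisposition groups. Nothing links these results to cell number.

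**The concern.** The Introduction gives the reason for looking at cell number: in obesity-prone rats, regain went together with the formation of new adipocytes. That is a statement about how many fat cells the animal or person has. A count of the cells in a needle sample is a different quantity. If it is reported as the number component of adipogenic capacity, a difference between the AA and TT groups, or a change between visits, could arise from the amount aspirated or from a change in cell size. Weight loss is expected to shrink fat cells, so the comparison before and after the diet is where a false sign of new cells is most likely. Up to 240 biopsies are planned (80 subjects × 3 visits), and as described they cannot answer the question about number.

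**Working it through.** The protocol states no figure for cell number, so there is none to reproduce. The sample size in 4.4 rests on resting energy expenditure and is unrelated.

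**Algebra, which needs no assumed values.** Let M be the aspirate mass, p the TAG fraction of the tissue, s the TAG per cell, N the subject's total adipocyte number and F the whole-body fat mass.

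1. TAG in the biopsy = pM.
2. Cells in the biopsy = DNA / 6 pg = pM / s. This rises in proportion to M, and N does not appear.
3. Mean cell size = pM / (pM / s) = s. M cancels, so size is sound.
4. The subject's cell number = F / s, because F = N × s when s represents all fat.
5. Count per gram of TAG = 1 / s. Dividing by the amount of sample removes M but leaves only the inverse of cell size.

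**Illustration 1: same person, different aspirates.** Assumed, not in the protocol: s = 0.6 µg and p = 0.8. For 0.25 g the count is 0.25 × 0.8 × 10^6 µg / 0.6 µg = 0.33 million.

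| Aspirate (g) | Count (million) | Size recovered (µg/cell) |
| --- | --- | --- |
| 0.25 | 0.33 | 0.600 |
| 0.5 | 0.67 | 0.600 |
| 1 | 1.33 | 0.600 |
| 2 | 2.67 | 0.600 |

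The count varies 8-fold and size does not move.

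**Illustration 2: shrinkage and new cells.** Fat masses and cell sizes are assumed.

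| Situation | F (kg) | s (µg) | Count per g TAG (million) | F / s |
| --- | --- | --- | --- | --- |
| Start | 35 | 0.600 | 1.67 | 5.83 × 10^10 |
| Shrinkage only | 25 | 0.429 | 2.33 | 5.83 × 10^10 |
| 20% more cells, same size | 42 | 0.600 | 1.67 | 7.00 × 10^10 |

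The per-gram count rises by 40% (2.33 / 1.67) when no cell has formed, and stays the same when 20% more have. F / s behaves correctly in both cases. The false rise is 1 / (1 − shrinkage) − 1: 11% for 10% shrinkage, 25% for 20%, and 40% for the 28.6% shown here.

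**Simulation.** Assumed: a coefficient of variation (CV) of 25% for the subject's cell number and 20% for cell size, independent of each other.

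| CV of aspirate mass | Correlation of count with N | with 1/s | with M |
| --- | --- | --- | --- |
| 0% | 0.00 | 1.00 | – |
| 10% | 0.00 | 0.89 | 0.45 |
| 30% | 0.00 | 0.55 | 0.82 |
| 50% | 0.00 | 0.36 | 0.91 |

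The zero correlation with N follows from the assumed independence. If number and size were related, the count would reflect N only through size, which is already reported.

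**The case against.** The strongest reply is that the protocol never says the raw count will be compared between groups or over time. In 7.3 the DNA step serves the calculation of cell size, and section 9.2 names no adipocyte variable. That is correct. A reader might infer that a raw-count comparison is planned, but the text does not establish it. What stands is that 7.1.1 promises a number, and 7.3 offers only this one. If the count is just a denominator, the number component has no derivation at all.

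A second reply is that 7.3 is an abbreviated account of a cited standard method, and that a laboratory manual or an analysis plan could add weighing or scaling. The title of reference 40 does concern cell number, though that of preadipocytes. Its content cannot be checked here, and 7.3 cites it for cell size. Scaling by sample weight would not be enough in any case, by step 5 above. The point is that the derivation given does not measure the endpoint named, which is more than an omitted detail.

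A third reply is that the proposed estimate carries its own assumption, because one abdominal site stands in for all fat. This is fair, and the estimate has to be labelled accordingly.

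**Conclusion.** The point holds as a mismatch between 7.1.1 and 7.3. The count in the aspirate is proportional to the amount aspirated and inversely proportional to cell size. Beyond what size already shows, it says nothing about the subject's adipocyte number. This follows from the protocol's own definitions. The 8-fold and 40% figures depend on assumed aspirate masses, cell sizes and fat masses, and show direction and possible scale only.

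Three stronger readings are not supported:

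- That true differences in cell number are merely diluted by sampling noise, so that variance or sample size rises by some factor. The count is not true number plus noise, and the protocol gives no CV from which to work out such a factor.
- That aspirate yield will change after weight loss. This may happen, but nothing in the protocol shows it.
- That the whole adipogenic-capacity endpoint fails. Mean cell size is a ratio in which sample mass cancels, and it stands as planned.

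The text should be corrected before cell number is analysed or reported.

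**What to change.** In 7.1.1 and 7.3, define the number component as estimated total adipocyte number: whole-body fat mass from the BodPod and deuterium measurement at the same visit, divided by mean TAG per cell, with both in the same mass unit. Apply it at the three biopsy visits: before weight loss, after weight loss and after maintenance. State that the count per biopsy, raw or per gram, is a step towards cell size and is not analysed as an endpoint. Leave mean cell size as it is.

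If the sponsor does not want to rely on this estimate, the alternative is to remove number from 7.1.1 and keep size alone.

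Neither option needs new data, because fat mass, TAG and DNA are already planned at those visits in the high and low groups. The cost of the first option is the assumption that abdominal subcutaneous cell size represents all fat depots. The result also combines two measured quantities and carries the error of both. It should be called an estimate wherever it is reported.
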